### Laboratory testing and sample handling

Initial trial visit

Ethylenediaminetetraacetic acid (EDTA) tube blood (1-1.5mL) for haematology (white cell count and differential, haemaglobin/haematocrit, platelet count) (
Table 2)Heparinised blood (2mL) for sodium, potassium, urea, creatinine, semi quantitative C reactive protein (CRP) test, bilirubin, aspartate transaminase (AST) and alanine transaminase (ALT)EDTA blood (2mL) will be used for malaria RDT, dengue RDT, scrub typhus RDT, and CRP RDT. Remaining blood centrifuged and plasma and blood pellet stored at -20°C /-80°C for future diagnostic, biomarker, pharmacokinetic studies and genetic analysis. Centrifugation and blood storage will be done ONLY if the patient fulfils the inclusion criteria.Blood culture (3-8mL depending on age). Urine sample will be collected from all participants and stored at -20°C/-80°C for later and tested by bioassay for antimicrobial activity.Faecal sample will be collected from all participants for standard bacterial culture (to detect
*S*. Typhi or Paratyphi). DNA (deoxyribonucleic acid) will be extracted from the stool and stored for later diagnostic microbiome studiesNasopharyngeal swab test to detect COVID-19 using a PCR test or as per current existing rules and regulations of the hospital. Sample collection will be carried out following all the guidelines of the local hospital for handling potential COVID-19 patients.Rapid diagnostic tests: - For the malaria and dengue NS1 antigen RDTs locally available tests will be used. The scrub typhus RDT will be Scrub Typhus Detect™ IgM Rapid Test (InBios, Seattle, USA). For CRP screening we will use a semi-quantitative lateral flow test (ACTIM CRP tests, Medix Biochemica) that uses a drop of blood and gives a result in 5 minutes. It has thresholds of 10, 40 and 80mg/L so will give the right cutoff for inclusion, and some information on how high CRP is when it is ≥10mg/L.

Follow up trial visits

A blood culture will be repeated at the day 7 follow up visit and at any time during follow-up if there is a clinical deterioration in the participant or a clinical suspicion of relapse after review and assessment by the trial physician. Stool cultures for
*S*. Typhi or
*S.* Paratyphi on day 0, 7, 14, 28. Also on day 90 if the day 0 blood/stool culture positive for salmonella.

### General comments

Blood samples drawn in the study clinic for diagnosis and confirmation of suspected typhoid fever will be handled, stored, processed, in accordance with standard operating procedures of the study Microbiology Laboratory. The results of these tests will be recorded in the participant CRF for use in this study.

Remaining samples will be stored at the local laboratory for further analysis, depending on funding availability, after the conclusion of the trial. This analysis will include diagnostic testing (serology or PCR) to determine additional causes of infection in the blood culture negative group.

Additionally DNA extraction for investigation of the genetic control of susceptibility to infectious diseases like typhoid and pharmacogenetic determinants may be carried out. DNA will be genotyped/sequenced and analysis will be performed (genome wide association study or GWAS analysis, and DNA sequence analysis).

At selected sites, additional samples will be taken for pharmacokinetic analysis. This will be one or two additional EDTA samples taken during the course of treatment. The cells and plasma will be separated and stored at -20°C/-80°C. These samples will subsequently be assayed for azithromycin and/or cefixime using high-performance liquid chromatography (HPLC). The data will be analysed using a population pharmacokinetic modelling approach using Pharmacokinetic/Pharmacodynamic Systems Analysis Software
ADAPT5.

Bacterial isolates will be stored at -20°C/-80°C for later whole genome sequencing. The WGS will be performed at study sites if they have capacity, or at the Wellcome Sanger Institute, UK. This will be to determine if recurrent positive blood cultures are due to relapse or re-infection, to understand the population structure of
*S*. Typhi/
*S.* Paratyphi across South Asia and characterise relevant resistance and/or virulence mechanisms.

### Sample size calculation

We will randomize 1500 subjects (750 per arm) within 2 years, with between 125 and 250 recruited per year at each site. Assuming a treatment failure risk of 15% in the group given azithromycin alone, the sample size will guarantee 92% power to detect an absolute risk reduction of 6% (from 15% to 9%) and 80% power to detect an absolute risk reduction of 5% (from 15% to 10%) in the group given the combined antimicrobials at the two-sided significance level of 5% allowing for up to 10% loss to follow up. In case of a lower treatment failure risk of 10% in the control arm, the trial will have 94% power to detect a 5% absolute risk reduction (from 10% to 5%) and 77% to detect a 4% reduction (from 10% to 6%).

### Statistical and analytical plans

The statistical aspects of the study are summarised here with details fully described in a statistical analysis plan (SAP) which will be finalised before any analysis takes place. The primary endpoint of this trial is the composite outcome of treatment failure by the 28th day after the initiation of treatment. Subjects who withdraw from the study prior to day 28 without treatment failure will be treated as right-censored. The primary comparison of the absolute risk of treatment failure until day 28 between the treatment arms will be based on Kaplan-Meier estimates and corresponding standard errors according to Greenwood’s formula.

The time to treatment failure from the onset of treatment will be described using Kaplan-Meier curves and compared between the treatment arms with a Cox proportional hazards model with treatment assignment as the primary covariate and adjustment for blood culture result (positive for
*S.* Typhi or
*S.* Paratyphi vs. negative), age (children (<16 years) and adults (≥16 years)), and country. Time to treatment failure from symptom onset will be analysed in the same way but subjects will be considered as left-truncated at the time of onset of treatment to account for the fact that they were not under observation before that timepoint.

Fever clearance time will be calculated using temperatures recorded twice per day and treated as an interval-censored outcome. The fever clearance time distribution will be estimated using the non-parametric maximum likelihood estimator (NPMLE) and comparisons between the arms will be based on a parametric Weibull accelerated failure time model. 

A two-sided significance level of 5% will be applied to all efficacy analyses. The primary analysis population for all analyses is the modified intention to treat (ITT) population consisting of all patients who have been randomised to the trial and received at least one dose of study treatment. Analysis will be according to the randomized treatment arm. Subjects, who were mistakenly randomised or withdrew before the first dose of study treatment was given, will be excluded. Subjects who were unblinded will be included in the ITT population.

The culture-confirmed population consists of all patients with blood-culture confirmed typhoid fever who received at least one dose of study treatment. Analysis will be according to the randomized treatment arm. The primary and secondary endpoints will be analysed both in the ITT and the culture-confirmed population. Planned sub-group analyses for the primary endpoint and fever clearance time include analyses by blood culture result (positive for
*S.* Typhi or
*S.* Paratyphi vs. negative), by age (children (<16 years) and adults (≥16 years)), by country, and by study site. 

A safety interim analysis will be conducted at 6 months and a combined safety and efficacy interim analysis will be conducted at 50% sample size, i.e. when outcome data from 750 subjects are available. Formal stopping for efficacy is only foreseen at the efficacy interim analysis in case of overwhelming efficacy for the combined treatment using the Haybittle-Peto boundary (p<0.001) as a guidance.

The efficacy interim analysis will also include a futility analysis which will assess the conditional power to detect a 6% difference in failure rates at the final analysis. If the conditional power is low, the DSMC may recommend closing the trial for futility or increasing its sample size. The final decision making in case of a sample size increase will require input from the Trial Steering Committee, the JGHT Committee and the joint funders. All analyses will be done with
R language for statistical computing version 3.6.2 software.

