** Participants will be randomly allocated to one of two treatment arms resulting in a 1:1 final disposition. The statistician in charge of randomization list preparation will set up statistical code to generate the randomization list and transfer it to the study pharmacist in accordance to the standard operation procedures (SOPs). The study pharmacist will then change the random seed, i.e. the initialization of the random numbers generator, in the statistical code in order to blind the biostatistician and then run the code to prepare the final randomization list. The generated randomization lists will be securely incorporated within the trial database. A reliable manual back-up system will also be available. The computer-generated randomisation list will use block randomization with stratification by site and age (children <16 years) and adults (≥16 years). The recruitment in most sites will take place during working hours as these are uncomplicated typhoid patients.

Randomisation will be performed using a web-based system accessed using an authorized username and password at each site and administered by the Oxford University Clinical Research Unit- Nepal Clinical Trial Unit independent from the study. Before treatment allocation the patient’s eligibility and informed signed consent will be confirmed and entered into the database. The allocation code will be held by the CTU pharmacist in Nepal.

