## Discussion

In this study, we will conduct a randomised comparison of azithromycin alone or azithromycin combined with cefixime for treating clinically suspected or confirmed uncomplicated typhoid fever at four sites across south Asia. We aim to test the hypothesis that the treatment failure proportion will be 15% with azithromycin alone but 9% if the azithromycin is combined with cefixime. When translated to the number of patients with typhoid fever across south Asia this improvement in outcome would make a substantial real-world contribution to improving the health of the population in our region. With an estimated 7 million people suffering from typhoid fever in South Asia each year
^
1
^, a 6% reduction in treatment failures in this population using this combination of drugs will mean at least 420,000 patients avoiding the need for further antimicrobial treatment and/or hospital admission, and consequently result in a lower financial burden and a reduced potential for onward transmission of the infection.

Cefixime and azithromycin are widely used antimicrobials in suspected or confirmed typhoid fever with excellent safety profiles. If the combination treatment is better than the single antimicrobial treatment, this will be an important result for patients across South Asia and other suspected typhoid endemic areas. We will also additionally investigate the financial implications for families and health system. Combined treatment may also limit the emergence of resistance if one of the components is active against resistant sub-populations not covered by the other antimicrobial’s activity. This is part of the rationale for using combination chemotherapy in other infections such as malaria, TB and HIV. In
*S.* Typhi and
*S.* Paratyphi A there are sporadic reports of resistance to both azithromycin and third generation cephalosporins
^
33,
34
^. The recent outbreak of MDR, fluoroquinolone and ceftriaxone resistant (XDR) typhoid in Pakistan is a warning of the potential for untreatable typhoid
^
35

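### Randomisation is stratified by site and age, but the primary day-28 Kaplan-Meier risk difference as written uses neither factor; if strata differ in risk, a little precision is lost, without harm to validity or the stated power

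*Protocol article*

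**What the plan says.** Under Study procedures (randomisation and treatment allocation), the article specifies "block randomization with stratification by site and age (children <16 years) and adults (≥16 years").

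Under Statistical and analytical plans, the primary analysis is fixed by estimator and variance. On the estimator it says: "The primary comparison of the absolute risk of treatment failure until day 28 between the treatment arms will be based on Kaplan-Meier estimates". For the variance it names Greenwood's method. No stratification or adjustment is mentioned there.

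The next paragraph does name adjusters for a secondary analysis. The Cox model for time to failure takes blood culture result plus "age (children (<16 years) and adults (≥16 years)), and country". It therefore includes age, and it has country where the randomisation had site. No covariates are listed for the Weibull model for fever clearance time.

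The section describes its content as "summarised here with details fully described in a statistical analysis plan (SAP) which will be finalised before any analysis takes place".

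The number of sites is unclear. The Discussion has "uncomplicated typhoid fever at four sites across south Asia", and recruitment is in four countries. The planned subgroup analyses, however, are "by country, and by study site", as separate items. The sample size section says: "We will randomize 1500 subjects (750 per arm) within 2 years, with between 125 and 250 recruited per year at each site".

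**The concern.** Blocking within site-by-age strata balances the arms on those factors, so differences in risk between strata contribute almost nothing to the real sampling error of the treatment comparison. A difference of two whole-arm Kaplan-Meier estimates with Greenwood errors treats each arm as one simple random sample and still counts that between-stratum variance. If strata differ in risk, the reported standard error exceeds the true one, the interval is too wide and the test falls below its nominal 5%.

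What is at stake is efficiency. The article's own power is 80% for 15% versus 10% and 77% for 10% versus 6%, so information the design has already secured is worth using. A smaller matter is consistency: if a country has more than one site, the Cox model leaves out part of a stratification factor.

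**Working it through.** **Inputs from the article.** 750 per arm, up to 10% loss, so n = 750 × 0.9 = 675 per arm; two-sided 5% (z = 1.96); control risk 15%; alternatives 9% and 10%.

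**The article's own power.** Two-proportion test, pooled variance under the null, no continuity correction, n = 675:

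- 15% vs 9%: 92.5% (stated 92%)
- 15% vs 10%: 79.4% (stated 80%)
- 10% vs 5%: 93.8% (stated 94%)
- 10% vs 6%: 77.4% (stated 77%)

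All four reproduce with an unstratified comparison.

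**Assumptions for the comparison.** The article gives no site- or age-specific risks. I take four equal sites, control risks c averaging 15%, and a common one-third relative reduction (e = 2c/3, so 15% vs 10%, d = 0.05). With no censoring before day 28 the Greenwood variance equals the binomial one, so binomial variances are used with n = 675.

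**Formulas.**

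- Crude: V_u = 0.15 × 0.85 + 0.10 × 0.90 = 0.2175; SE_u = √(0.2175/675) = 0.01795.
- Stratified: V_s = mean over sites of c(1−c) + e(1−e), which equals V_u − Var(c) − Var(e), with Var(e) = (4/9)Var(c); SE_s = √(V_s/675).
- Between-site share of control outcome variance: f = Var(c)/(0.15 × 0.85).
- True size of the crude test: 2[1 − Φ(1.96/√(1−f))].
- True power of the crude test: Φ((d − 1.96·SE_u)/SE_s), because the design already reduces the real sampling error to SE_s and only the critical value is inflated. Stratified test: Φ(d/SE_s − 1.96).
- Per-arm size m at which the crude test matches the stratified power: √m = √675 + 1.96(√V_u − √V_s)/d; the gain in total is 2(m − 675).

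| Assumed site control risks | Var(c) | f | V_s | SE_s | Crude SE too wide by | Crude size | Power, crude → stratified | Worth in patients (total) |
|---|---|---|---|---|---|---|---|---|
| 15% at all sites | 0 | 0 | 0.2175 | 0.01795 | 0 | 5.0% | 79.5% → 79.5% | 0 |
| 10/13/17/20% | 0.00145 | 1.1% | 0.2154 | 0.01786 | 0.5% | 4.9% | 79.66% → 79.93% | about 9 |
| 5/10/20/25% | 0.00625 | 4.9% | 0.2085 | 0.01757 | 2.1% | 4.4% | 80.0% → 81.2% | about 40 |
| 3/8/19/30% | 0.01085 | 8.5% | 0.2018 | 0.01729 | 3.8% | 4.0% | 80.4% → 82.4% | about 70 |

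Worked example, third row: √m = 25.981 + 1.96 × (0.46637 − 0.45659)/0.05 = 26.364, so m = 695 and 2 × (695 − 675) = 40.

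**At the headline effect (15% vs 9%, e = 0.6c, d = 0.06, V_u = 0.2094)** the gains are smaller: V_s = 0.2074, 0.2009 and 0.1946 give 92.7% → 92.8%, 93.0% → 93.6% and 93.3% → 94.2%.

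**Site-by-age strata.** Eight equal strata evenly spaced from 2% to 28% make the crude SE 2.4–2.5% too wide, inside the range above.

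**Number of sites.** 125–250 per site per year for two years is 250–500 per site; 1500/500 = 3 and 1500/250 = 6. The recruitment rate is compatible with four sites and also with more sites than countries.

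**The case against.** The best defence is that the article is a summary and leaves detail to a SAP that is not shown. Wording that bases the comparison on Kaplan-Meier estimates does not exclude stratum weighting, and a crude marginal risk difference is valid and transparent. Much of this stands: a stratified version may already be in the SAP. Even so, the article names the estimator and the variance formula for the primary analysis and lists adjusters for the Cox model. What it fixes for the primary comparison does not reflect the randomisation.

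Several stronger readings are tempting but not supported:

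- *The trial is underpowered or the test invalid.* All four stated powers come from an unstratified calculation, and size stays at or below 5%.
- *The loss is established.* It depends on heterogeneity the article does not report. The Discussion mentions ceftriaxone-resistant typhoid in Pakistan, but the control arm receives no cephalosporin, so that bears mainly on the effect of adding cefixime and not on control-arm risk. The azithromycin clinical failure range of 0–18% in the Introduction is across studies, not trial sites.
- *The gain is worth 16, 70 or 125 patients.* Those figures follow from 1350 × f/(1−f), which uses the null variance ratio. Matched on power, they are about 9, 40 and 70.
- *The Cox standard errors are too wide.* Omitting a prognostic factor from a Cox model mainly pulls the hazard ratio towards 1. That model is secondary and already includes age.
- *Site is missing from the Cox model.* With one site per country, country and site coincide and nothing is omitted. The Discussion's four sites, and the Study status section's reference to Pakistan as a site, point that way; the separate subgroup listing points the other way.
- *Country should also be replaced in the Weibull model.* The article lists no country term there.

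**Conclusion.** The point holds as a modest matter of efficiency and consistency. The primary comparison, as written, does not use the factors by which patients are randomised. If failure risk differs between strata, the crude standard error is 0.5% to about 4% too wide and stratifying adds about 0.3 to 2 points of power for 15% versus 10%, under assumed site risks from 10–20% to 3–30%, four equal sites, 675 evaluable per arm and a common one-third relative reduction. With homogeneous strata there is no gain. The sample size and the type I error need no correction. The Cox remark applies only if some country has more than one site, which the article leaves unclear.

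**What to change.** Before unblinding, define the primary estimate in the SAP as the day-28 Kaplan-Meier risk difference computed within site-by-age strata and combined with stratum-size (Mantel-Haenszel-type) weights. Combine the Greenwood variances across strata with the squared weights, and prespecify how sparse strata are pooled, for example within country. Keep the crude difference as a supporting analysis.

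State the number of sites per country. If any country has more than one, use site (as strata or covariate) in place of country in the secondary Cox model; if each has one, no change is needed there.

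The cost is SAP wording, a few lines of R code and the need to settle a pooling rule in advance. No new data are required.

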## Introduction

Typhoid (caused by
*Salmonella enterica* serovar Typhi) and paratyphoid fever (caused by
*Salmonella enterica* serovar Paratyphi A), collectively referred to as typhoid fever in this protocol, are common causes of non-specific febrile infection in adults and children presenting to health care facilities in low resource settings such as the South Asia region
^
1–
4
^. South Asia has been described as the largest hub for typhoid fever in the world and antimicrobial resistance has become a critical issue
^
5
^. In the last 20 years, treatment of typhoid fever with a 7-day course of a single oral antimicrobial, such as ciprofloxacin, cefixime or azithromycin, given in an out-patient setting has led to patient recovery in 4 to 6 days without the need for expensive hospitalization. Increasing antimicrobial resistance in Asia and sub-Saharan Africa threatens the effectiveness of these treatments and increases the risk of prolonged illness and severe disease.

The fluoroquinolone class of antimicrobials have been a common choice to treat typhoid fever across South Asia during the last two decades. Now low and high-level resistance is so widespread that the entire class is no longer a reliable treatment choice
^
2,
6
^. Cefixime and azithromycin are commonly recommended alternatives and widely used
^
7–
11
^, but the conflicting results from small randomised controlled trials (RCTs) with cefixime and azithromycin in typhoid fever leave many clinicians unsure about the optimum antimicrobial treatment for typhoid fever in this region.

The outcome for patients treated with cefixime (10–20mg/kg/day for 7–14 days) in typhoid fever are particularly mixed with prolonged fever clearance times of 6–8 days, clinical failure rates of between 6% and 27% and microbiological failure rate between 0% and 4.5%
^
12–
15
^. The reported fever clearance times with azithromycin treatment (10–20 mg/kg/day for 5–7 days) is usually 4–6 days and clinical failure rates range from 0% to 18% with a microbiological failure rate from 0% to 3.2%
^
7,
16–
23
^. A number of the studies with azithromycin have demonstrated a delayed microbiological clearance, indicated by positive blood culture during the treatment course
^
17,
19–
21,
23
^. Azithromycin activity is predominantly intracellular with studies from Vietnam indicating that up to one third of
*S.* Typhi may be found in the extracellular compartment
^
24,
25

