*S*. Paratyphi on day 0, 7, 14, 28. Also on day 90 if the day 0 blood/stool culture positive for salmonella.
^4^If still febrile on day 7 twice daily assessments will continue until afebrile for48hrs and further treatment may be required as determined by the Trial Physician] PCR=polymerase chain reaction, COVID-19=coronavirus disease 2019, RDT=rapid diagnostic test. *37.5 degrees C axillary temperature.

**
*Follow-up trial visits.*
** There will be routine participant follow-up via telephone or face-to face contact twice a day for the first seven days of antimicrobial treatment (and longer if the symptoms have not resolved). Caregivers are instructed to be consistent and measure temperature always at the same location (oral or axillary, not either or) for each patient and approximately at the same time. Face to face follow up by participant attendance at the clinic will be at 7 days, two weeks and one month. For patients who had positive blood or stool culture for
*S.* Typhi or
*S*. Paratyphi at the time of presentation there will be a final clinic follow-up at three months.

The telephone calls will be made to ensure that clinical progress is satisfactory and for monitoring of symptoms. Any problems faced by participants can be discussed and possible adverse effects identified.

Community medical assistants (CMA) will visit the patients at their home on day 2 and day 4 of treatment to ensure that clinical progress is satisfactory and for monitoring. Special attention will be paid to the assessment of adherence to study medications, drug-related adverse events and disease related events. Adherence will be assessed using standardised questionnaires and pill counts. At the first visit their home location will be recorded using global positioning system (GPS).

All patients will return to the clinic for follow-up on day 7, day 14, day 28 (and day 90 if typhoid fever confirmed at onset) after the start of treatment for follow up clinical history, physical examination and sampling.

To ensure an optimal retention rate, the participants will be contacted by phone to remind them of their next visit. In addition, patients who have missed a visit will be contacted by phone for a maximum of three times after which a maximum of three home visits can be conducted. All contact attempts will be recorded.

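### Fever clearance time is compared by a Weibull model alone, so with its default standard error the 5% level is assured only if clearance times are Weibull

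*Protocol article*

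**What the plan says.** All references are to the Protocol article; the SAP is not shown.

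- Statistical and analytical plans, on the data: "Fever clearance time will be calculated using temperatures recorded twice per day and treated as an interval-censored outcome". The FCT distribution is to be estimated by the non-parametric maximum likelihood estimator (NPMLE).
- Same sentence, on the arms: "comparisons between the arms will be based on a parametric Weibull accelerated failure time model". No other between-arm method for FCT is named.
- Same section, on the level: "A two-sided significance level of 5% will be applied to all efficacy analyses". Primary and secondary endpoints are analysed in the ITT and culture-confirmed populations, and FCT also by blood culture result, age, country and site.
- Table 2, footnote 4, on follow-up of fever: "If still febrile on day 7 twice daily assessments will continue until afebrile for48hrs".
- The section presents itself as a summary and leaves the detail to the SAP.

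The article gives no distribution for FCT. The Introduction only reports that clearance on azithromycin usually takes 4 to 6 days.

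**The concern.** The objective is to compare FCT between arms, so the null hypothesis is that both arms share one distribution, whatever its shape. The default Weibull test takes its standard error from a narrower hypothesis: that the shared distribution is Weibull. If it is not, the standard error can be wrong even when the arms are identical. With a tail longer than Weibull it is too small, because the Weibull estimate gives each patient a weight that grows steeply with clearance time, and slow clearers vary more than the model allows.

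A non-Weibull shape is plausible here. The ITT population mixes culture-positive and culture-negative febrile illness, children and adults, and four countries, and a mixture of Weibull distributions is generally not Weibull. At stake is a p-value or interval for FCT that claims a difference in clearance too often, in the main analysis and again in the culture-confirmed and subgroup analyses. A larger sample does not cure it.

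**Working it through.** **Inputs from the article.** Two-sided 5% level; half-day observation grid (temperatures twice daily); 750 per arm; up to 10% loss, so 750 x 0.9 = 675 per arm. With 675 per arm the article's power figures for the primary endpoint reproduce: 92.5%, 79.4%, 93.8% and 77.4% against the stated 92%, 80%, 94% and 77%. For FCT the only stated figure is the 5% level.

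**Assumptions.** Shape of the FCT distribution; median about 4.5 days; default (model-based) standard error.

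**Analytic check, log-normal times, no censoring.**

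1. Let z = (log t - mu)/sigma. The Weibull score for location is proportional to exp(z) - 1, and the model takes Var(exp(z)) = 1.
2. The fitted values satisfy E[exp(z)] = 1 and E[z exp(z)] - E[z] = 1. If z is normal with mean m and variance s^2, the first gives m = -s^2/2. The left side of the second is (m + s^2) - m = s^2, so s = 1 whatever the spread of log t.
3. Hence Var(exp(z)) = e - 1 = 1.718, and the true SD is sqrt(1.718) = 1.311 times the model standard error.
4. Type I error = 2 x (1 - Phi(1.96/1.311)) = 13.5%, so a nominal 95% interval covers about 86.5%. Sample size does not enter.

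**Simulation under no treatment effect.** Interval-censored Weibull likelihood on the half-day grid, Wald test. Rejection in %; a dash means not run.

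| Common distribution | Per arm | Followed to | Default SE | Robust SE | Rank-type test |
|---|---|---|---|---|---|
| Weibull, shape 2.4 | 675 | day 28 | 5.2 | 5.3 | 5.4 |
| Weibull, shape 1.8 | 750 | day 28 | 4.7 | 4.7 | - |
| Gamma, shape 5 | 675 | day 28 | 8.3 | 5.1 | 5.3 |
| Gamma, shape 3 | 750 | day 28 | 7.5 | 5.2 | - |
| Log-normal, log-SD 0.40 | 675 | day 28 | 12.9 | 5.2 | 5.0 |
| Log-normal, log-SD 0.50 | 675 | day 28 | 14.0 | 6.4 | 5.1 |
| Log-normal, log-SD 0.50 | 750 | no limit | 14.1 | 5.6 | - |
| Log-normal, log-SD 0.50 | 750 | day 28 | 12.9 | 5.5 | 4.9 |
| Same, 10% dropout | 750 | day 28 | 13.1 | 5.3 | - |
| Log-normal, log-SD 0.50 | 750 | day 14 | 10.0 | 5.0 | - |
| Log-normal, log-SD 0.50 | 750 | day 7 | 6.5 | 5.1 | - |
| Log-normal, log-SD 0.70 | 750 | day 28 | 11.4 | 5.2 | - |
| Log-normal, log-SD 0.50 | 200 | day 28 | 15.5 | 6.9 | - |
| Log-logistic, scale 0.25 | 675 | day 28 | 21.4 | 6.8 | 6.9 |
| Log-logistic, scale 0.30 | 750 | day 28 | 18.1 | 5.7 | - |
| Log-logistic, scale 0.30 | 750 | no limit | 24.9 | 7.1 | - |

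Runs numbered 1,500 to 10,000 per row. At 1,500 runs the Monte Carlo standard error at 5% is sqrt(0.05 x 0.95/1500) = 0.6 points. The 200 per arm is an assumed culture-confirmed size.

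**Mixtures.** Five mixtures of faster and slower fevers, each component exactly Weibull, with assumed proportions and medians, gave 6.5%, 7.1%, 7.5%, 10.2% and 11.4%. The highest values came from a 15-20% minority of slow clearers.

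**Direction.** In one log-normal run with 12.8% rejection, 6.3% favoured the combination (nominal 2.5%); the remaining 6.5% favoured azithromycin alone.

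**Power for a 7% shorter FCT (time ratio 0.93).** Weibull truth: default 89%, robust 89%, log-rank 89%. Log-normal truth (log-SD 0.40): default 88% (not a valid 5% test), robust 76%, log-rank 88%.

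**The case against.** **The shape is unknown.** The article gives no FCT distribution, and right skew alone does not produce the problem: Weibull times are themselves right-skewed and give about 5%, gamma 6-8%. A reader might infer that the planned test rejects 13% of the time in this trial. The documents do not support that; the figure belongs to a log-normal tail followed to clearance. This stands.

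**Follow-up to clearance is not settled for the analysis.** Footnote 4 makes it plausible that slow clearances are observed. But Assessment of endpoints makes patients febrile on day 7 treatment failures, with rescue if appropriate, and the article does not say whether FCT is censored at rescue or failure. With censoring at days 7-9, log-normal inflation falls to about 5-8%. This stands as a condition.

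**The article names a model, not a variance estimator.** The SAP may specify a robust standard error or a check of fit, and silence on these is not an error in a condensed article. This stands. What the article does fix is the parametric model as the sole basis of the comparison.

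**A Weibull model is a recognised choice.** It suits interval-censored data and gives a readable time ratio. Describing the data with the NPMLE and comparing arms with a model is not a contradiction; the same section pairs Kaplan-Meier curves with a Cox model. True, but this does not protect the type I error.

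**The consequence is limited.** A reader might infer a bias towards the combination, or a threat to the main result. Neither follows: the excess is two-directional, and the primary Kaplan-Meier comparison, sample size and interim rules do not use this model.

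**Conclusion.** The concern holds as a conditional one. The planned FCT comparison, with the default standard error, is assured its 5% level only under a Weibull shape. The excess beyond 5% needs three things together: a common distribution with a heavier tail than Weibull (log-normal or heavier to reach about 13%), model-based standard errors, and little censoring of slow clearers. Under those conditions the two-sided type I error is about 13-15% for log-normal times (11.4% in one wider-spread case) and about 18-25% for log-logistic. It is about 10% for log-normal censored at day 14, about 5-8% for log-normal censored at days 7-9, about 6-8% for gamma, and 5% if Weibull is true. The documents do not settle which case applies, so this is not a proven wrong figure. It concerns a secondary endpoint and is a cheap improvement.

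**What to change.** In Statistical and analytical plans, or in the SAP before it is finalised:

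- Take the FCT p-value from an interval-censored (generalised) log-rank test, which needs no parametric shape and matches the planned NPMLE.
- Keep the Weibull time ratio as the effect estimate, with a robust (sandwich) standard error and confidence interval.
- Apply both in the ITT, culture-confirmed and subgroup FCT analyses.

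The cost is a sentence of text and a few lines of R, with no new data or patients. In the simulations above, log-rank power equalled that of the planned test. There are two downsides. The robust interval is wider when the shape is not Weibull. If the arms differ, the log-rank p-value and the interval for the time ratio may not agree exactly, so the plan should say that the test decides and the time ratio describes.
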